#### Rationale for outcome measures

As a primary outcome measure, the ABC-I was selected. The ABC is a caregiver-completed rating scale for assessing problem behaviors in children and adults, which has robust psychometric properties in intellectually impaired and developmentally delayed populations [50, 64, 65]. The empirically derived and widely used irritability subscale consists of 15 items and comprises items reflecting temper outbursts, aggression, negative affect, and self-harm behavior. Irritability has been identified as a prominent behavioral correlate of ASD. The ABC-I has often been used as an outcome measure in treatment studies of behavioral problems in individuals with ASD and ID [66–68]. The ABC, including the irritably subscale, has been shown to be sensitive to treatment change in previous clinical trials of FXS [69, 70]. The other domains of the ABC, including lethargy/social withdrawal, stereotypic behavior, hyperactivity/noncompliance, and inappropriate speech, will serve as generalization measures to evaluate transfer effects of the intervention to a broader domain of functioning [71]. A generalization measure is an outcome measure that is related to the target behavior (irritability), for example irritability at school and at home (another setting), or interventional effects on a completely different behavior, such as less hyperactive when the target behavior is irritability.

By including an extensive set of secondary outcome measures in this study, we aim to explore the effectiveness of CBD on several behavioral and psychiatric domains as it is yet unclear which manifestations specifically respond to treatment. Moreover, we aim to explore if these outcome measures are appropriate and useful in these patient groups and in RGNDs in general. We chose outcome measures at different levels, such as disorder-specific, personalized and generalizable measures. As most of our patients will have ID, proxy-rated outcome measures applicable to children as well as adults were selected that have been psychometrically considered valid tools to measure aberrant behavior, anxiety, mood, ASD features, and parental stress in ID.

The CGI scale is a well-established rating tool applicable to all psychiatric disorders that can easily be used by the practicing clinician and provides an assessment of the clinician’s view of the patient’s global functioning prior to and after initiating a study medication [48]. The CGI has two components: the CGI-Severity (CGI-S) which rates illness severity, and the CGI-Improvement (CGI-I) which rates change from the initiation (baseline) of treatment. The CGI can track clinical progress across time and has shown to correlate well with standard, well-known research drug efficacy scales and longer, more tedious and time consuming rating instruments across a wide range of psychiatric diagnoses [72, 73]. However, the CGI is not goal-oriented and changes do not provide mechanistic insight. We will be utilizing the CGI to evaluate the overall clinical picture, encompassing various aspects of a patient’s functioning, which extend beyond behavioral domains. To address potential concerns related to inter-rater reliability, we have implemented training protocols for all investigators and clinicians involved in the study. Additionally, we will have the same rater conduct assessments for individual patients throughout the trial, which allows for a relative assessment of changes within each patient, facilitating the detection of meaningful shifts in their overall clinical presentation over time.

Additionally, available syndrome-specific outcome measures will be included for both TSC (TSC-PROM) and MPS III (SBRS). These PROMs focus on syndrome-specific targets that are of relevance to these patients and their functioning and quality of life. A recent validation study of the PROM for adults with TSC has shown that it is a reliable and valid instrument to measure the impact of the disease on functioning, which can be used in clinical and research settings to systematically gain insight into patients’ experiences [51]. It covers the physical, mental health domain, activities and participation and environmental factors, addressing the impact of specific TSC manifestations on adult patients’ health-related quality of life (QoL). The SBRS is developed to assess the behavioral phenotype in children with MPS III and its progression and results from treatment over time [52]. The SBRS is validated in 25 children with MPS IIIA, aged 2 to 18 years old [74]. As there is no specific questionnaire on QoL for FXS and children with TSC, the PedsQL will be used, which is a practical, brief, standardized, generic assessment tool to measure health-related QoL. Next to the pediatric version, an adults version exists which will be used for adults [53].

The ADAMS, considered a psychometrically sound instrument among individuals with ID [54], will be used to screen for symptoms of anxiety, depression and mood disorders.

The SCQ (originally the Autism Screening Questionnaire (ASQ)) will be used to assess the severity of ASD symptoms [75–78]. The SCQ current version will be used as it enables us to screen for ASD, to compare overall levels or severity of ASD symptoms, and to assess current ASD symptoms and change over time in both young and older children, adolescents, and adults.

The SRS-2 is a widely used measure of ASD symptoms for social behavioral problems in children and adults [56]. It may not be suitable for patients with a developmental age below four years. It will therefore be filled out when applicable, depending on the developmental age as assessed by the VABS-III during baseline [62].

The SSP is a commonly used shortened form of Dunn’s Sensory Profile caregiver questionnaire [79], containing 38 items measuring sensory features, organized into seven subscales. The total score will be used to measure sensory functioning [80].

Reducing severe behavioral manifestations may have benefits for family and caregivers. Therefore, we chose the parenting stress questionnaire (OBVL) which is applicable to children of all ages and has been validated for institutions for youth care, including mild ID as well [58].

Furthermore, GAS and the PQ enable us to focus on personalized and for participants relevant targets, also reflecting the treatment target [59, 81]. GAS is an individualized outcome measure, involving goal selection and scaling standardized to calculate the extent to which an individual’s goal is met. Patients and caretakers will select their own specific goals together with their treating physician/therapist. It is a measurement instrument that is very sensitive to change, in particular in small and heterogeneous patient populations [59]. The PQ is used as a symptom list to compare assessments of personalized goals with those measured by GAS [60]. Adding the PQ allows us to compare outcomes of standardized and personalized tools.

In case participants have epilepsy, a seizure diary will be used to evaluate change in seizure frequency.

Hepatic enzyme levels (ALT, AST, and bilirubin) will be checked to monitor adverse effects.

### Trial procedures

During the N*-of-*1 trial, the final CBD dosage as determined by the dose titration phase or placebo will be administered twice daily. During washout periods, no study medication will be taken.

#### N-*of*-1 trial: multiple crossover phase

Prior to the start of the trials, the participant and substitute decision maker(s) will be seen at the clinic to discuss the procedure and sign for informed consent (Fig. 2). Personalized goals with regard to GAS will be identified together with the treating physician, psychologist, patients and primary caregivers. Seizures semiology will be discussed in detail and classified according to the classification of the International League Against Epilepsy (ILAE) [82]. Reporting of seizure frequency (by patients or caregivers) will be assessed. The shortened version VABS-III will be filled out by the clinicians to determine whether the SRS-2 could be filled out during the trial [62]. Optionally, fE/I EEG recordings will be performed at baseline.

**Fig. 2 Fig2:**
[figure not shown]
Time schedule of enrolment, interventions, and assessments. Crosses (X) indicate research steps to be conducted. Underlined crosses (X) indicate assessments via phone calls. ABC, Aberrant Behavior Checklist; ADAMS, Anxiety, Depression, and Mood Scale; CBD, cannabidiol; CGI, Clinical Global Impression; EEG, electroencephalogram; GAS, Goal Attainment Scaling; OBVL, parenting stress questionnaire; PedsQL, Pediatric Quality of Life Inventory; PQ, personal questionnaire; SCQ, Social Communication Questionnaire; SSP, Short Sensory Profile; SRS-2, Social Responsiveness Scale; VABS-III, Vineland Adaptive Behavior Scale-III

A 2-week baseline period will follow without any intervention. The ABC, CGI, syndrome-specific outcome measures, ADAMS, SCQ, SRS-2 (if applicable), SSP-NL, and OBVL, will be filled out and seizures will be reported. These questionnaires can be completed within one hour. For children, the OBVL will be filled out by parents or primary caregivers if they have known the child for at least six months. The CGI can be completed in less than a minute by an experienced rater. A dose titration phase is followed by a taper period and washout period. During the dose titration phase, contact moments will take place (by phone) twice weekly, and hepatic enzyme levels will be measured. The individual N*-of-*1 trial consists of two cycles each containing one active treatment (A), one placebo treatment (B), run-in periods, taper periods, and washout periods. Medication will be administered at home, institution setting or day care by caregivers. The ABC irritability subscale will be filled out weekly by primary caregivers, which can be completed within a few minutes. The other outcome measures will be scored once during the baseline period, at the end of each interventional (including placebo) period, with a total of five measurements, and if participating in the optional extension phase at the follow-up measurement. Adverse effects will be assessed as well. The questionnaires can be filled out digitally (Castor EDC), phone or on paper forms. Caregivers will be asked to report all seizures in the seizure diary. To reduce burden, assessments occur by phone calls except for the clinical visits. During the experiment, it will be attempted to not switch rating caregivers.

#### Optional open-label extension phase

In consultation with the primary caregivers, patients may continue with CBD treatment during an optional one-year open-label extension phase after which a final contact moment takes place. At this follow-up measurement, questionnaires will be filled out again and personalized goals will be evaluated.

### Safety evaluation

#### Adverse events

Adverse events (AEs) will be monitored throughout the N*-of-*1 trials. All SAEs and Suspected Unexpected Serious Adverse Reactions (SUSARs) occurring during the study and either reported spontaneously or as part of the AE monitoring will be followed up by the principal investigator and will be reported separately to the Medical Ethics Committee (MEC). Unblinding will occur if there is reason to believe a SAE or SUSAR was due to the study medication and if the patient cannot be treated without knowing which treatment they were receiving. Unblinding and the reason for unblinding will be recorded. AEs, SAEs and SUSARs will be followed until they have abated or a stable situation has been reached.

#### Removal from the trial and replacement of participants

Participants will be removed from the study if informed consent is withdrawn. The investigator can decide to withdraw a participant from the N*-of-*1 trial for urgent medical reasons. Participants with hepatic enzyme level elevations sex times or greater the levels measured during baseline will be excluded, as this is a known potential for drug-induced liver injury with CBD.

In case of a drop-out, completed weeks before withdrawal will still be analyzed and a new participant will be recruited with a newly randomized sequence.

#### Premature termination of the study

The study will be terminated prematurely if more than one participant indicates a great burden of switching between placebo and CBD periods accompanied by serious safety concerns.

#### Data Safety Monitoring Board (DSMB) and monitoring

Independent qualified monitors from the Clinical Monitoring Center (CMC) will monitor the study.

Because of the small sample size and the close monitoring of patients, it was not necessary to set up a DSMB.

### Analysis

#### Data collection and management

All data will be collected and handled in accordance with applicable privacy and data protection regulations. We will collect the data according to the FAIR principles (Findable, Accessible, Interoperable, Reusable) [83]. Trial-specific documents and the Case Report Forms (CRFs) will be securely stored with restricted access limited to nominated research staff.

Assessments will be entered in the CRFs set up in Castor Electronic Data Capture (EDC). All questionnaires can be filled out digitally (Castor EDC) or by using paper forms. Automatic reminders will be sent when a questionnaire has not been completed on time. Participant burden will be limited as much as possible by using a subscale of the ABC for weekly questionnaires and having contact moments by video-conference or phone instead of a visit.

A participant identification code list will be used with unique participant identifiers not deducible to participants. Only four investigators and a methodologist and biostatistician will have access to the key and source data. Data will be stored for 25 years in a secured database and body material will be stored for 5 years.

#### Statistical methods

Individual treatment effects for participants will be quantified as summary statistics. A mixed model analysis will be applied for statistically testing the effectiveness of the intervention at group level combining data from the individual N*-of-*1 trials [84]. The mixed model will account for between-subjects heterogeneity in interventional effects by including a random treatment effect.

The mean treatment effect on the primary outcome irritability subscale of the ABC will be estimated and tested using a linear mixed model. The model will contain a fixed effect for the average treatment effect (CBD or placebo), random effects for patients, cycle within patient, and treatment (within patient). A mixed model analysis with similar model structure will be performed for the secondary study parameters. Because of the many data points per period, small amounts of missing data will not pose problems for the mixed model analysis, assuming missingness is random. The Imer package of R will be used for mixed model analyses. An analysis based on a summary measure will be performed if issues such as singularity arise. A two-sided significance level of 5% will be used.

fE/I EEG data will be processed offline using the Neurophysiological Biomarker Toolbox [85], an open-source MATLAB toolbox for the computation and integration of neurophysiological biomarkers. With this toolbox, a wide array of resting state parameters can be evaluated including power spectra and coherence and has been applied to neurological clinical studies. The data processing will be performed using MATLAB 7.12.0 software (The MathWorks Inc., Natick, MA, R2022a).

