MPS III is an autosomal recessive lysosomal storage disorder caused by a deficiency of 1 of 4 enzymes involved in the degradation of the glycosaminoglycan heparan sulphate. Four types, caused by deficiencies of the different enzymes, are recognized: MPS III type A, B, C and D, with MPS IIIA the most frequent subtype [23]. As a group, MPS III comprises 47% of all MPS cases diagnosed and the combined birth prevalence is 1.89 per 100.000 live births [24]. It is characterized by progressive intellectual neurologic deterioration (PIND) [25] and severe and progressive behavioral and sleeping problems including restless, destructive, chaotic, anxious and sometimes aggressive behavior [26]. There is yet no curative treatment [23]. To date, no evidence exists for the efficacy of CBD for MPS III, although a potential treatment approach has been described that focuses on modulation of the endocannabinoid system in lysosomal storage disorders including MPS III [27].

FXS is a relatively more common genetic disorder associated with ID. It is X-linked, occurs in approximately 1:4000 males and 1:8000 females, and is caused by an alteration in the recently renamed Fragile X Messenger Ribonucleoprotein 1 (*FMR1*) gene containing a CGG-repeat with repeat length exceeding 200 CGGs [28, 29]. Other manifestations include ADHD (70%), ASD (60%), and anxiety (80%). A recent trial with transdermal CBD gel showed good efficacy on irritability in children with FXS [9]. The role of the endocannabinoid system in FXS, its dysregulation due to the absence of Fragile X Messenger Ribonucleoprotein (FMRP), and the potential role of CBD has been previously described [13, 30]. The endocannabinoid system facilitates synaptic homeostasis and plasticity through the cannabinoid receptor 1 (CB1) on presynaptic terminals, resulting in feedback inhibition of neuronal signaling, which are thought to be disrupted in FXS and may be restored by CBD acting as a negative allosteric modulator of CB1 [31]. These findings suggest that the endocannabinoid system may be involved in the neurodevelopment and behavior regulation.

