**Fig. 1 Fig1:**
[figure not shown]
Study design of the N*-of-*trial. CBD, cannabidiol; FU, follow-up

The total duration of each trial will last around 1 year. The optional open-label extension phase will be a further 12 months.

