### Sample size

The sample size calculation was based on a summary measures analysis of the treatment effect [49]. The difference between the mean irritability ratings of the Aberrant Behavior Checklist (ABC) in CBD periods and placebo periods was used as a summary measure for the treatment effect in an individual participant. Heussler et al. [9] reported a standard deviation (SD) of 12 points for single ratings on the subscale. This estimate for the SD includes both within- and between-subject variance. The intraclass correlation coefficient (ICC) was assumed to be 0.75. In addition to the estimate for the within-subject variation of the outcome measure, an a priori estimate was needed for the between-subject variation of the treatment effect. Assuming an SD of 3 points for the SD of the random treatment effect, 95% of the subject-specific treatment effects roughly falls within a range of 12 points. Based on the estimate assuming two cycles with six ABC ratings within each period and assuming a two-sided significance level of 5%, a total of 6 participants will yield 80% power to detect a mean difference of 6 points between intervention and placebo periods, corresponding to a mean difference of 0.5 times the SD as reported by Heussler et al. [9]. As effects for pediatric and adult population may differ, separate power analyses were performed for the pediatric and adult cohorts. Per cohort, this amounts to 6 pediatric patients and/or 6 adult patients, with a total inclusion of 12 patients with TSC, 12 with FXS and 6 pediatric patients with MPS III. MPS III is a type of childhood dementia and most patients never reach adulthood [26]. Adult patients experience progressive dementia. This stage of the disease is not associated with severe behavioral manifestations, and therefore we will not include adult patients with MPS III.

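### The primary model has no fixed time term, so drift within a cycle costs precision in 6-patient cohorts and offsets some individual effects

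*Protocol article*

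**What the plan says.** Under Statistical methods, the primary ABC-I model has one fixed effect, treatment: "The model will contain a fixed effect for the average treatment effect (CBD or placebo), random effects for patients, cycle within patient". The rest is random: "random effects for patients, cycle within patient, and treatment (within patient". Secondary outcomes get a similar structure. The fallback is a summary measure, with no time adjustment stated: "An analysis based on a summary measure will be performed if issues such as singularity arise". Individual effects are also to be reported as summary statistics.

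Elsewhere the article gives reasons to expect that time may matter. On duration: "The total duration of each trial will last around 1 year". The Background describes MPS III as marked by "severe and progressive behavioral and sleeping problems including restless, destructive, chaotic, anxious and sometimes aggressive behavior". Study design and duration sets out two cycles, each with one CBD and one placebo period of 6 weeks, plus 3-week run-ins, 2-week tapers and 1-week washouts. Sample size powers cohorts of six separately: "a total of 6 participants will yield 80% power to detect a mean difference of 6 points between intervention and placebo periods". MPS III consists of one such cohort.

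**The concern.** A random cycle effect lets the level differ between cycle 1 and cycle 2. It does not describe change from the first to the second period inside a cycle, and those periods start about 12 weeks apart (6 + 2 + 1 + 3). If ABC-I scores drift over that time, whichever treatment comes second takes the drift. A participant whose order is the same in both cycles carries one full period of drift into the CBD-placebo difference. A participant whose order is reversed carries none.

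Four things are at stake:
- the precision of cohort estimates based on six people;
- a chance shift when the realised orders are unbalanced;
- the variance of the random treatment effect, which takes up order-related drift and makes response look more variable than it is;
- individual effects, which the Discussion offers as a basis for treatment decisions and which averaging over participants cannot repair.

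**Working it through.** **Inputs (Sample size section).** SD of a single rating 12; ICC 0.75; SD of the random treatment effect 3; two cycles with six ratings per period; n=6; target difference 6 points. Statistical methods: "A two-sided significance level of 5% will be used".

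**The plan's own figure.** Residual variance = 144 × (1 − 0.75) = 36. Each participant has 12 ratings per condition, so the variance of the CBD-placebo difference = 9 + 36/12 + 36/12 = 15. The paired t-test (noncentral t, n − 1 df) gives power 0.855 at n=6 and 0.737 at n=5. Six is the smallest n that reaches 80%, so the stated sample size reproduces.

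**Drift by sequence.** Let ABC-I change by b points per 12-week period, the same for everyone. This is an assumption; the article gives no trend. With periods numbered 1 to 4 (A = CBD, B = placebo):
- ABAB: (1+3)/2 − (2+4)/2 = −1, an offset of −b
- BABA: an offset of +b
- ABBA and BAAB: (1+4)/2 − (2+3)/2 = 0, no offset

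If order is drawn independently per cycle, the four sequences are equally likely. The offset then has mean zero and variance b²/2.

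**Cohort power.** The difference variance becomes 15 + b²/2:

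| b per period | variance | SE, n=6 | power, n=6 | power, n=12 |
|---|---|---|---|---|
| 0 | 15.0 | 1.58 | 0.855 | 0.998 |
| 2 | 17.0 | 1.68 | 0.811 | 0.995 |
| 3 | 19.5 | 1.80 | 0.758 | 0.989 |
| 6 | 33.0 | 2.35 | 0.541 | 0.908 |

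Power at n=6 drops below 0.80 at about b=2.2. Pooled n=30 stays above 0.99 throughout. Simulating the discrete orders instead of using the variance formula gives 0.52 to 0.53 at n=6, b=6.

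**Spacing.** If the run-in lies inside the 6-week period, successive periods are 9 weeks apart. A weekly drift of 0.25 points is then b=2.25 rather than 3, with power 0.80; 0.5 per week is b=4.5 rather than 6, with power 0.65.

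**Bias and type I error.** In simulation with random order, mean bias is about 0 and type I error about 5% for drifts from 0 to 0.5 points per week. If orders are forced to balance across a cohort, the shift is zero but the test is conservative (type I error 3.0% at 0.25 and 1.0% at 0.5 per week), and power is 77% and 52%.

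**Chance shift.** Six participants give 12 cycle orders. Drawn independently, they balance exactly with probability 22.6% and split 8:4 or worse with probability 38.8%. An 8:4 split shifts the estimate by (8 − 4)/12 × b = b/3, or 1 point at b=3.

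**Apparent heterogeneity.** At b=3, b²/2 = 4.5 is added to a true treatment-effect variance of 3² = 9, an increase of 50%.

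**Individual effects.** The sampling SE of one participant's difference is √(36/12 + 36/12) = 2.45. At b=3, a same-order participant is offset by 3 points, more than that SE and half the 6-point target.

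**Effect of adjusting.** With a fixed linear week term and no trend, the SE at n=6 is 1.59 to 1.60 against 1.58. With the term, SE stays near 1.6, type I error at 4.8 to 5.2% and power at about 85% for every drift from 0 to 0.5 per week.

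**The case against.** A reader might infer that the omitted term biases the primary comparison or invalidates its test. The documents do not support this. Every cycle holds both treatments, so drift between cycles cancels in complete data. Order is randomised, so drift within a cycle has mean zero, and its variance passes through the random treatment effect into the standard error. The test keeps its level. That part of the objection stands in full.

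The size of any loss also rests on a trend the article never gives. From period 1 to period 4, b=3 means 9 points and b=6 means 18 points, which is 0.75 and 1.5 of the plan's SD of 12, shared by all participants. The word progressive is used of MPS III behaviour only, 6 of 30 participants, with no rate over one year. The Sample size section adds that the later dementia stage is not linked to severe behavioural problems, so steady worsening is not assured. TSC and FXS have 12 participants each and lose little. The 12-week spacing, and the 38.8% and 50% figures, depend on readings of the design and of the block randomisation that the article does not settle. These points limit the severity.

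It could also be said that the analysis plan may add the term. The article, however, does not leave the model open: it lists the terms, and time is not among them.

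**Conclusion.** The point holds as one of precision. The listed model leaves within-cycle drift unmodelled in a trial of about a year per participant. Under an assumed common linear drift, 12-week spacing and independent cycle orders, power in a 6-patient cohort stays at or above 80% up to about b=2.2, then falls to 0.76 at b=3 and 0.54 at b=6. With 9-week spacing the loss is smaller. Disorder-level analyses at n=12 and the pooled analysis stay above 0.90 even at b=6. The consequences fall mainly on MPS III, on the six-person age cohorts, on the estimated variation in response, and on individual effects for participants with the same order twice. A conclusion that the sample size is wrong, or that the trial cannot proceed without this change, would go further than the documents allow. It is a worthwhile improvement at very low cost, not a must-fix error.

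**What to change.** Prespecify a fixed linear time term (week or period number) in the primary and secondary mixed models, with disorder-specific slopes when disorders are pooled. At cohort level it costs about 1 df and, with no trend, an SE of 1.59 to 1.60 instead of 1.58. A four-level period factor is more flexible but dearer (SE 1.68 to 1.82), so the linear form is the better primary choice at n=6.

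A time term in the group model does not by itself correct effects computed participant by participant. For the individual effects and the summary-measure fallback, estimate the common slope from the weekly ratings and subtract it before taking each participant's CBD-placebo difference. Do not regress six patient differences on an order score: that lowers power to about 73% with unrestricted orders (81% with balanced orders), against 85% for the plain analysis when there is no trend.

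The remaining limit is the assumption of a slope that is linear and common within a disorder. The change is a few sentences, to be fixed before unblinding; the sample size stays as it is.

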### Outcome measures

The primary outcome is a change on the irritability subscale score of the Aberrant Behavior Checklist (ABC-I) during active interventional periods compared to placebo periods.

Secondary outcome measures include:Total ABC [50];CGI [48];Syndrome-specific outcome measures, including the TSC-specific patient-reported outcome measure (TSC-PROM) [51] and the Sanfilippo Behavior Rating Scale (SBRS) [52];Pediatric Quality of Life Inventory (PedsQL) [53];Anxiety, Depression, and Mood Scale (ADAMS) [54];Social Communication Questionnaire (SCQ) [55];Social Responsiveness Scale (SRS)-2 (when appropriate) [56];Short Sensory Profile (SSP-NL) [57];Parenting Stress Questionnaire (OBVL) [58];Goal Attainment Scaling (GAS) [59];Personal Questionnaire (PQ) [60];Focal and generalized seizure frequency;Adverse effects;Hepatic enzyme levels.

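### The primary outcome's mixed-model structure, run in a linear-model routine, is extended to all secondary outcomes without exception, and suits seizure counts and adverse effects poorly

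*Protocol article*

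**What the plan says.** All statements are from the protocol article.

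- **Statistical methods.** The irritability subscale of the Aberrant Behavior Checklist (ABC-I) is analysed by a linear mixed model with a fixed treatment effect and random effects for patient, cycle within patient and treatment within patient. The text continues: "A mixed model analysis with similar model structure will be performed for the secondary study parameters". On software: "The Imer package of R will be used for mixed model analyses" (that is, lmer). On failure of the model: "An analysis based on a summary measure will be performed if issues such as singularity arise". On missing data: "Because of the many data points per period, small amounts of missing data will not pose problems for the mixed model analysis".
- **Outcome measures.** The secondary list includes "Focal and generalized seizure frequency", adverse effects and hepatic enzyme levels, alongside the rating scales.
- **Rationale for outcome measures.** "In case participants have epilepsy, a seizure diary will be used to evaluate change in seizure frequency".
- **N-of-1 trial: multiple crossover phase.** ABC-I is rated weekly. For the rest: "The other outcome measures will be scored once during the baseline period, at the end of each interventional (including placebo) period".

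No count model, binary model, exposure offset or transformation is named for any outcome.

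**The concern.** Seizure counts exist only for participants with epilepsy, cannot fall below zero, and can differ between people by orders of magnitude. A treatment that cuts everyone's seizures by the same proportion produces raw differences proportional to each person's own rate. On an additive scale one or two high-frequency participants then determine both the mean difference and its standard error. A consistent effect can be missed, and the interval for the mean difference can be too narrow in exactly those samples that happen to contain no high-frequency participant.

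Adverse effects are events, possibly few in placebo periods, so a constant-variance Gaussian model is again a poor description.

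Seizure frequency and adverse effects are both named secondary objectives under Aim and objectives. The Background puts epilepsy at 85% in TSC. If that rate applied to the 12 planned TSC participants, about 0.85 × 12 = 10.2 would contribute seizure data.

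**Working it through.** **1. The plan's own figure.** There is none for the secondary outcomes. The Sample size section, for ABC-I, does reproduce. The variance of a participant's CBD-minus-placebo mean is 3² + 36 × 2/12 = 15, where 36 = 12² × (1 − 0.75) and 12 is two cycles of six ratings. With n = 6, a 6-point effect and a two-sided 5% t-test, power is 85.5% (73.7% at n = 5), so six is the smallest number reaching 80%.

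**2. Data points per period.** ABC-I has six ratings per period in that calculation; the other scales have one. If the same variances held for a once-per-period score (an assumption), the variance becomes 3² + 36 × 2/2 = 45 and power at n = 6 falls to 43%. One missed form then loses the whole period, not one rating in six.

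**3. Seizures, hand example (assumed counts).** Placebo counts are 2, 5, 10, 20, 60 and 200, and every participant is reduced by exactly 30%.
- Differences: 0.6, 1.5, 3, 6, 18, 60.
- Mean = 89.1/6 = 14.85; SD = 23.02; SE = 23.02/√6 = 9.40.
- t = 14.85/9.40 = 1.58 on 5 df, p = 0.175.

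Every participant has the same rate ratio of 0.70, yet the raw-scale test does not detect it. The example is deliberately extreme: with identical ratios the log scale has no variance at all. It shows the mechanism only.

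**4. Seizures, simulation (assumed rates).** Counts are negative binomial, with a median of 20 per period, an SD of the log patient rate of 0.8 to 1.6, a rate ratio of 0.6, and some variation of the effect between participants. The raw-scale analysis is the paired difference of participant means, which is the treatment contrast of the balanced linear mixed model when its random-treatment variance is not estimated at zero. Coverage is for the true mean difference in counts. For example, at log-rate SD 0.8 and an SD of the log effect of 0.3, the true value is 20·e^(0.32) × (0.6·e^(0.045) − 1) = −10.26.

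| n with epilepsy | Coverage of raw-scale 95% interval | Power, raw scale | Power, log-rate scale |
|---|---|---|---|
| 6 | 71–91% | 6–16% | 27–28% |
| 12 | 74–92% | 17–39% | 54–57% |
| 30 | 80–92% | 42–79% | 93–95% |

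A separate simulation with the same median, rate ratio and spread of rates gave, at n = 6, coverage of 66–91% and power of 9–27% against 41–46%. The levels depend on further assumptions the protocol does not supply, such as overdispersion within a participant; the direction does not change. With no treatment effect the raw-scale t-test rejected in 1.2–4.0% of trials, so it is conservative.

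**5. The fallback.** A raw-scale summary measure per participant is the very quantity analysed in step 4, so switching to it leaves these results unchanged. Its stated trigger is also singularity and similar issues; skewness is not named.

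**6. Adverse effects (assumed rates).** Suppose an event occurs in 5–10% of placebo periods and 30% of CBD periods.
- Binary variance ratio: (0.30 × 0.70)/(0.05 × 0.95) = 4.4, or 0.21/(0.10 × 0.90) = 2.3.
- Chance that a six-participant cohort (12 placebo periods) has no placebo event: 0.95¹² = 54%, or 0.90¹² = 28%.

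Interval coverage for adverse effects was not computed.

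**The case against.** **The word linear is attached only to the primary outcome.** The sentence on secondary parameters speaks of similar structure, which could mean the same fixed and random effects inside a generalized model, and link functions are commonly left to an analysis plan. This stands in part: the linear reading is inferred. But the article makes an all-inclusive statement and then names a linear-model routine for its mixed models, so the natural reading is a Gaussian model for every secondary outcome. If something else is meant, the text should say so.

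**The secondary outcomes are largely exploratory and the primary conclusion is untouched.** True, and the raw-scale test would not generate false seizure claims. This limits the weight of the point.

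**A reader might infer that the model also gives wrong error bars for the once-per-period scales.** The documents do not support that. With four on-trial values per participant, the variance components are pooled over participants: n − 1 df for treatment by patient, n for cycle within patient and n for residual. They are estimable, though poorly at n = 6. In balanced data the treatment test is essentially a paired t-test. At n = 6, simulated fits were singular in 55–62% of cases, but the protocol provides a fallback for exactly this, and type I error was about 5% under it. With t degrees of freedom the mixed model gave about 4%. A figure of about 8% arises only with a Wald z test, which the protocol does not specify.

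**A logistic model can also fail with sparse adverse effects.** Correct: cohorts with no placebo event produce separation. The replacement must allow for this.

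**Conclusion.** The point holds for seizure frequency and, more qualitatively, for adverse effects. Extending the primary model to these outcomes without exception costs power for seizures and gives raw-scale intervals that under-cover, roughly 66–92% against a nominal 95% across 6 to 30 participants, without inflating type I error. The stated fallback does not repair this on the raw scale. For adverse effects the mismatch rests on unequal variances and empty cells under assumed event rates; invalid intervals have not been demonstrated.

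The missing-data sentence is accurate only for weekly ABC-I. For the once-per-period scales this is a matter of wording and precision, not of validity.

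The sizes rest on assumed seizure and event rates and on reading the secondary models as linear. The full protocol or an analysis plan, not shown here, may already specify outcome-specific models. The change is worth making because it is cheap and the present wording commits to the less suitable method.

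**What to change.** 1. Limit the sentence on secondary parameters to approximately continuous scores.
2. Seizures: in participants with epilepsy, use a negative binomial or log-rate mixed model with offset log(diary days), and report a rate ratio with its interval.
3. Adverse effects: describe them by treatment period, or use a binary or count model with a method that tolerates sparse or zero cells.
4. Restrict the missing-data remark to the weekly ABC-I, and note that for the other scales one missed form loses a period.

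The cost is wording in the protocol or analysis plan, with no new data. The small downside is having more than one type of model to specify and report.
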